## Abstract

**Introduction:**

Acquired premature ejaculation (APE) is a common male sexual dysfunction characterized by a clinically significant reduction in intravaginal ejaculatory latency time. In China, its prevalence ranges from 4% to 39%, while globally, approximately 26% of men report premature ejaculation (PE), with APE accounting for 18.8% of cases. The mechanisms of APE remain unclear, with psychological factors (e.g., anxiety, depression) and neurological factors identified as key influences. Selective serotonin reuptake inhibitors (SSRIs), such as paroxetine, delay ejaculation by elevating synaptic 5-HT levels, but they are associated with side effects and poor compliance. Chaihu-Shugan-San (CHSGS), a classical Traditional Chinese Medicine (TCM) formula for depression and anxiety, is commonly used in TCM andrology for APE. It is hypothesized that CHSGS alleviates APE symptoms by improving emotional states through central nervous system modulation.

**Methods and analysis:**

This is a randomized, blinded interventional trial with four parallel groups. A total of 84 eligible participants will be randomly assigned to one of four groups: the paroxetine group, CHSGS group, CHSGS + paroxetine group, or placebo group. The primary outcomes are Intravaginal ejaculatory latency time (IELT) and Pre- and post-treatment brain fMRI scans. The Secondary Outcomes include Premature ejaculation profile (PEP), Chinese Index of Premature Ejaculation (CIPE) and TCM syndrome score.

**Ethics and dissemination:**

The trial has been registered with the International Traditional Medicine Clinical Trial Registry (Registration No. ITMCTR2025000309) and Ethics Committee of Chongqing Hospital of Traditional Chinese Medicine (Registration No. 2023-ky-87). It will be proceeded in the Departments of Urology and Radiology at Chongqing Traditional Chinese Medicine Hospital in Chongqing, China.

**Trial registration number:**

ITMCTR2025000309.

## Strengths and limitations of this study

Focuses on central nervous mechanisms of acquired PE using fMRI, investigating how CHSGS may improve symptoms via CNS modulation, addressing gaps in APE neurobiology research.

Combines clinical metrics (IELT) and fMRI to evaluate both behavioral and central nervous system mechanisms, with secondary measures including PE-specific scales and TCM syndrome scores.

Uses daily paroxetine instead of on-demand dapoxetine, potentially affecting comparability due to different administration modes.

CHSGS is a multi-ingredient formula, making it difficult to isolate active components or single targets, limiting mechanistic analysis to macro-level brain activity changes.

## Introduction

Premature ejaculation (PE) is a prevalent form of male sexual dysfunction, characterized by ejaculation occurring earlier than desired during vaginal sexual intercourse. In general, we categorize premature ejaculation into two types: lifelong PE, which occurs every time or almost every time from the first sexual experience onwards, and acquired PE (APE), which develops after a period of sexual activity without any ejaculation issues. In APE, there is a clinically significant and bothersome reduction in the time to ejaculation, often reduced to 3 min or less (Salonia et al., 2021). Among the Chinese population, the prevalence of PE ranges from around 4%–39%. Globally, about 26.0% of men report experiencing PE, with APE making up 18.8% of these cases (Yang et al., 2023). Due to embarrassment and lack of awareness, the possible prevalence of PE is generally underestimated, and men with PE often experience severe psychological difficulties, avoid physical and emotional intimacy, and fall victim to false medical advertisements and unproven medical management (Shindel et al., 2025).

The mechanism of PE is currently unclear, and psychological factors are an important influence, but there is growing evidence that neurological factors are a complex influence (Yuan et al., 2025), and studies in animal models and with clinical experience have found that neurological factors are one of the most important factors in premature ejaculation (Aru et al., 2023). The brain expresses rich and dynamic patterns of neural activity across multiple spatial and temporal scales (Gul et al., 2022), and the developmental process of PE also involves multiple brain regions and systems, with complex and highly coordinated relationships among them (Wu et al., 2024). Previous animal studies have proposed a central control mechanism for ejaculatory dysfunction (Liu et al., 2025), It is currently believed that the possible neural mechanisms of PE are due to dysfunction of somatosensory centers and dysregulation of neurophysiological aspects (Ma et al., 2019).

Selective serotonin reuptake inhibitors, such as dapoxetine and paroxetine, have been shown to delay ejaculation. Paroxetine, as a selective 5-hydroxytryptamine (5-HT) reuptake inhibitor, can regulate central nervous activity by elevating the level of 5-HT in the synaptic gap, inhibit the ejaculatory reflex from the spinal cord level, improve the control of ejaculation, and prolong the ejaculatory latency period (Raveendran and Agarwal, 2021). Emerging research indicates that paroxetine administration could modulate neurofunctional dynamics in major depressive disorder, particularly influencing amygdala reactivity and functional connectivity patterns within associated neural networks (Tassone et al., 2024). However, these medications carry the risk of side effects and can be expensive. As a result, many patients have poor compliance, which makes it much more difficult to treat the disease (Niu et al., 2024).

Traditional Chinese medicine (TCM) is regarded as an effective treatment for APE. Unlike Western medicine, TCM requires a holistic approach, tailoring treatment based on the patient’s overall physical condition. In a multicenter survey conducted in China, the intervention rate of TCM for PE reached 39.4% (Sansone et al., 2024). Current literature has demonstrated that the occurrence of APE is linked to psychological disorders, particularly anxiety and depression (Yang et al., 2019). Chaihu-Shugan-San (CHSGS) is a classical prescription to treat depression, Several research teams have confirmed through both clinical studies and animal experiments that CHSGS has a significant effect in alleviating depression and anxiety (Zhu et al., 2022; Zhang et al., 2024; Liu et al., 2020). More studies have focused on the mechanisms by which CHSGS improves depression, and current evidence suggests that the antidepressant properties of CHSGS appear to mediate through multiple interrelated biological systems, including monoaminergic neurotransmission, hypothalamic-pituitary-adrenal axis regulation, brain-derived neurotrophic factor, synaptic remodeling mechanisms, gut-brain axis interactions, and inflammatory pathway modulation. The compound likely exerts its therapeutic effects via multimodal mechanisms involving both direct modulation of these core pathophysiological targets and indirect interactions with downstream molecular effectors, such as receptor systems, intracellular signaling cascades, and epigenetic regulators, with predominant actions localized to central neurochemical processes (Guo et al., 2024). In the clinical practice of TCM andrology, this herbal formula is also commonly used in clinical practice for the treatment of APE. Thus, we hypothesized that CHSGS could alleviate symptoms of APE and enhance patients’ quality of life by improving their emotional state though central nervous system.

Therefore, in this protocol, we plan to perform a double-blind randomized controlled trial, aiming to:1. Compared with the placebo and paroxetine, CHSGS will be as the same effective to the treatment for APE.2. Compared with paroxetine alone, CHSGS and combination of drugs will be more effective due to its specific effects.3. Investigate the influence of paroxetine or/and CHSGS capsule treatment on the brain activities of patients with APE compared with that of placebo treatment by fMRI and analyze the possible correlations between the changes of cerebral activity and the improvement of clinical variables in each group so as to explore how the paroxetine and CHSGS capsule manages depression by modulating brain function to treat APE.

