## Methods

### Study design

This study will be a blinded interventional trial with four parallel groups and a natural control group. The study will be conducted in accordance with the Declaration of Helsinki and follows the Consolidated Standards of Reporting Trials statement for randomized trials, as well as the Standard Protocol Items: Recommendations for Interventional Trials (SPIRIT). The trial has been registered with the International Traditional Medicine Clinical Trial Registry (Registration No. ITMCTR2025000309) and Ethics Committee of Chongqing Hospital of Traditional Chinese Medicine (Registration No. 2023-ky-87), and will be proceeded in the Departments of Urology and Radiology at Chongqing Traditional Chinese Medicine Hospital in Chongqing, China. According to the minimum requirements for network analysis of functional neuroimaging studies, 15 subjects were needed in each group, and 21 subjects were included in each group to ensure the credibility of the study results, taking into account the unavailability of data due to patient dropout and head movement during scanning (Desmond and Glover, 2002). Through previous studies and in combination with the actual situation of the project (Rodríguez Del Águila and González-Ramírez, 2014), a total of 84 subjects were included in this study, and they will be equally divided into the following four groups: paroxetine group; CHSGS group; CHSGS + paroxetine group; placebo group. In addition, we will recruit 15 healthy volunteers as natural control group (Figure 1).

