### Paroxetine group

Patients will be provided three-daily treatment with 5 g mixed starch powder added to the 5 red capsules and one-daily treatment with 30 mg paroxetine added to the yellow capsule each time until 4 weeks.

Dapoxetine and paroxetine are both 5-HT reuptake inhibitors for the treatment of premature ejaculation, however, dapoxetine is not recommended for daily administration, so that it is therefore difficult to observe its effects on the central nervous system. Also a trail showed that an on-demand dose of 30 mg dapoxetine is no more effective than the currently prescribed paroxetine treatment (Simsek et al., 2014). So we choose paroxetine as the positive control group as well as the treatment group. Smashed paroxetine will be mixed with starch powder and stir well into a container in order to be made into capsule.

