### Primary outcome

Drawing on a range of clinical studies, the assessment will be carried out on all patients. Specifically, for patients with APE (Premature Ejaculation), the mean changes from the baseline (the day when the patient commences the protocol) to the end of the observation period (the day when the protocol concludes) will be evaluated in two aspects: the brain MRI and the intravaginal ejaculatory latency time (IELT) measured using a stopwatch, which has been extensively applied and is recommended as a primary outcome measure in clinical trials for APE.

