### Data analysis

#### Clinical variables analysis

Two blinded evaluators will conduct the analysis of clinical data using SPSS 22.0 (SPSS Inc., Chicago, IL). Missing data analysis will be carried out in accordance with the intention - to - treat (ITT) principle, taking into account the baseline characteristics.

The clinical scores of the subjects will be examined through Pearson correlation analysis. All clinical data in this study will be presented in the following ways:1. Continuous measurement data will be presented as the mean ± standard deviation (SD), along with the mean, SD, median, and interquartile range.2. Categorical data will be presented as counts and percentages.

The following analysis tools will be employed: the Cochran - Mantel - Haenszel (CMH) test or nonparametric test, an independent samples t - test, and a two - sided test. Additionally, analysis of covariance, covariance analysis, generalized estimating equations, chi - square (
$x^{2}$
) tests, and linear regression will be applied to all available and appropriate data. A P - value <0.05 will be considered statistically significant.

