Premature ejaculation is a common male sexual dysfunction disorder, which is closely related to the central nervous system (Waldinger, 2006). In terms of neurotransmitters, an imbalance of serotonin, dopamine, and others can affect ejaculation. For example, abnormalities in serotonin - related receptors, an increase in glutamate concentration in the thalamus, and a decrease in GABA receptor expression are all associated with premature ejaculation (Andersson and Abdel-Hamid, 2011). There are many structural and functional abnormalities in brain regions such as the thalamus, frontal lobe, and somatosensory cortex. These include changes in the gray matter volume, local morphology, and functional connectivity of the thalamus, alterations in the thickness of the frontal lobe, gray matter volume and functional connectivity of specific regions, as well as abnormal related indicators in the somatosensory cortex. In addition, the thalamus - frontal lobe - somatosensory cortex circuit is also abnormal, such as a decrease in functional connectivity in some regions and a reduction in short functional connectivity density (Wu et al., 2024). These changes in the central nervous system collectively influence the occurrence and development of premature ejaculation (Chen et al., 2020). Unfortunately, however, much of the current research on premature ejaculation has focused on lifelong premature ejaculation, while relatively little research has been done on acquired premature ejaculation (Lu et al., 2020). Therefore, we hope to reveal the central nervous mechanism of acquired premature ejaculation and the intervention mechanism of Chinese medicine for acquired premature ejaculation (Xu et al., 2024).

In order to guarantee the reliability of the result of this study, we adopt the quality key point control as follows:

Subject Selection Criteria: For the purpose of baseline homogeneity, the patients in this study are restricted to those aged between 18 and 70 years old.

Sample Size Determination: To achieve stable statistical power, the sample size is carefully planned. In each group, 21 patients will be included for clinical evaluation, and 15 healthy volunteers will be included for the central mechanism study. The latter group will also undergo MRI scans.

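### Aims 1 and 2 conflict as written, and the equivalence wording of aim 1 cannot be supported by the listed difference tests or by 21 patients per arm

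*Protocol article*

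**What the plan says.** All references are to the protocol article.

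- **Introduction, aim 1:** "Compared with the placebo and paroxetine, CHSGS will be as the same effective to the treatment for APE".
- **Introduction, aim 2:** "Compared with paroxetine alone, CHSGS and combination of drugs will be more effective due to its specific effects".
- **Introduction, closing hypothesis before the aims:** CHSGS is expected to relieve APE symptoms.
- **Paroxetine group:** "So we choose paroxetine as the positive control group as well as the treatment group".
- **Primary outcome:** change from baseline in two things, "the brain MRI and the intravaginal ejaculatory latency time (IELT) measured using a stopwatch".
- **Study design:** "According to the minimum requirements for network analysis of functional neuroimaging studies, 15 subjects were needed in each group", and then "21 subjects were included in each group to ensure the credibility of the study results", with dropout and head movement during scanning given as the reasons for the increase. The total is 84.
- **Clinical variables analysis:** a CMH or nonparametric test, "an independent samples t - test, and a two - sided test", plus analysis of covariance, generalized estimating equations, chi-square tests and linear regression. P<0.05 is the only criterion given.
- **Discussion, sample size paragraph:** "To achieve stable statistical power, the sample size is carefully planned". No power, effect size or SD is attached to this statement.

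**The concern.** Three parts of the text do not fit together.

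1. CHSGS alone cannot be both as effective as paroxetine (aim 1) and more effective than it (aim 2). Aim 1 also puts placebo in the same sentence. This clashes with the hypothesis that CHSGS works and with the use of paroxetine as positive control.
2. A claim of equal effect needs a procedure that can reject a difference of a stated size. The listed procedures, judged at P<0.05, can only reject no difference.
3. The sample size was not derived from IELT, yet the Discussion describes it as giving stable power.

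At stake is the main clinical conclusion. The article hopes to provide an evidence-based treatment option. A statement that CHSGS is as effective as paroxetine would matter to patients, and this design cannot deliver it.

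**Working it through.** **The plan's own figure.** 4 × 21 = 84, which reproduces. The 15 and the step to 21 cannot be derived, because no effect size, SD, power, margin or loss rate is given. As arithmetic, 15/(1 − d) = 21 implies d = 28.6%.

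**The aims side by side**

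| Comparison | Aim 1 | Aim 2 | Elsewhere |
|---|---|---|---|
| CHSGS vs placebo | same | – | CHSGS hypothesised to relieve symptoms (Introduction) |
| CHSGS vs paroxetine | same | CHSGS better | paroxetine is positive control (Paroxetine group) |
| Combination vs paroxetine | – | combination better | – |

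The second row is the direct conflict. The first row conflicts with the stated hypothesis.

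**What 21 per arm can show.** Inputs: n = 21 per arm (Study design); two-sided 0.05 (Clinical variables analysis). Assumptions: results in SD units of the analysed outcome, equal SDs, unadjusted comparison of two arms, all 21 per arm analysed.

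- Standard error of a pairwise difference: √(2/21) = 0.309 SD.
- 95% CI half-width: t(0.975, 40) × 0.309 = 2.021 × 0.309 = 0.62 SD.
- Chance of a non-significant t-test, from the noncentral t with 40 df and noncentrality δ√(21/2):

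| True difference (SD) | Non-significant |
|---|---|
| 0.3 | 84% |
| 0.5 | 65% |
| 0.6 | 52% |
| 0.7 | 40% |
| 0.8 | 28% |
| 1.0 | 11% |

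- Difference detectable with 80% power: 0.89 SD (noncentral t). The normal approximation, (1.960 + 0.842) × 0.309, gives 0.86 SD.

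**What margin equivalence would need.** Two one-sided tests (TOST) at 5% each, true difference 0, 80% power.

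- Smallest margin, normal approximation: (1.645 + 1.282) × 0.309 = 0.90 SD. Simulation with the t distribution gives 78% power at 0.90 SD, so about 0.9 SD or slightly wider is the limit.
- At an assumed margin of 0.5 SD, power with 21 per arm is about 4% by simulation; the normal approximation gives 0.
- At that margin, n per arm for 80% power is 2 × (2.926/0.5)² = 68.5, so 69. At 0.8 SD it is 27, and at 1.0 SD it is 18.

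**The case against.** **Language.** The aims are ungrammatical, and part of the conflict may be loose wording. A reader might infer that the trial expects CHSGS to be inert and paroxetine to equal placebo. The documents do not support that as the intention, given the hypothesis of benefit and the positive-control role. Aim 2 might also mean only the combination arm. That would remove the conflict over paroxetine, but the sentence names CHSGS separately, and the placebo wording and the equivalence problem would remain.

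**Non-significance read as sameness.** A reader might infer that a non-significant test will be reported as equal effect. The article nowhere says so; it only defines what counts as significant. What stands is narrower: it gives no valid route to the conclusion in aim 1.

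**Any result confirms an aim.** This is also tempting, but it goes too far. A result in which CHSGS is significantly worse than paroxetine supports neither aim.

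**Deferral to the full protocol or SAP.** A margin and an interval rule may be set there, and their absence from an article is not the point. The conflicting aims are in this text, and with 21 per arm an added margin would have to be about 0.9 SD or wider.

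**The figures.** No IELT SD or important difference is given, so 0.5 SD is an illustration, and missing a real deficit becomes less likely as the deficit grows (28% at 0.8 SD). It is tempting to quote power at 15 per arm, but 15 is an imaging minimum and the allowance above it partly covers head movement, which does not remove an IELT value. Analysis of covariance is listed and would help: with an assumed baseline correlation of 0.5 to 0.7, the detectable difference is 0.886 × √(1 − r²), about 0.77 to 0.63 SD. These limits stand, and the SD figures should be labelled as unadjusted and assumed.

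**Conclusion.** The concern holds in this form. Aims 1 and 2 contradict each other as written, and aim 1 contradicts the article's own hypothesis about CHSGS. The equivalence wording is not matched by any listed analysis. With 21 per arm, equivalence is within reach only for a margin of about 0.9 SD or wider, and a true 0.5 SD deficit would be missed about 65% of the time. The claim of stable power has no stated basis for IELT. The contradiction and the mismatch of claim and test rest on the text alone. The sizes rest on SD units, an unadjusted two-arm comparison and full data in 21 per arm. The finding does not depend on any prediction of how the investigators would interpret a non-significant result.

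**What to change.** In the Introduction, restate each comparison with its hypothesis type:

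1. CHSGS superior to placebo on IELT.
2. The combination superior to paroxetine alone on IELT.
3. CHSGS versus paroxetine reported as an estimate with its 95% CI, with a statement that no equivalence or non-inferiority conclusion will be drawn from a non-significant test.

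In the sample size paragraph of the Discussion, replace the stable-power wording. Say that the size comes from the imaging minimum and that, for IELT, 21 per arm gives 80% power for a pairwise difference of about 0.89 SD in an unadjusted two-sided t-test, and for a smaller difference with baseline-adjusted analysis of covariance.

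**Cost.** Wording only; recruitment and procedures are unchanged. The sponsor gives up formal claims that CHSGS is as effective as paroxetine or better than it. If superiority over paroxetine is truly intended, keep it as an explicit superiority hypothesis and delete the equal-effect wording.

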## Methods

### Study design

This study will be a blinded interventional trial with four parallel groups and a natural control group. The study will be conducted in accordance with the Declaration of Helsinki and follows the Consolidated Standards of Reporting Trials statement for randomized trials, as well as the Standard Protocol Items: Recommendations for Interventional Trials (SPIRIT). The trial has been registered with the International Traditional Medicine Clinical Trial Registry (Registration No. ITMCTR2025000309) and Ethics Committee of Chongqing Hospital of Traditional Chinese Medicine (Registration No. 2023-ky-87), and will be proceeded in the Departments of Urology and Radiology at Chongqing Traditional Chinese Medicine Hospital in Chongqing, China. According to the minimum requirements for network analysis of functional neuroimaging studies, 15 subjects were needed in each group, and 21 subjects were included in each group to ensure the credibility of the study results, taking into account the unavailability of data due to patient dropout and head movement during scanning (Desmond and Glover, 2002). Through previous studies and in combination with the actual situation of the project (Rodríguez Del Águila and González-Ramírez, 2014), a total of 84 subjects were included in this study, and they will be equally divided into the following four groups: paroxetine group; CHSGS group; CHSGS + paroxetine group; placebo group. In addition, we will recruit 15 healthy volunteers as natural control group (Figure 1).

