### Regional homogeneity analysis

SPM12 was used to conduct a regional homogeneity analysis of the resting - state imaging data. First, a paired t - test was used for the comparative analysis of the ReHo images of the APE subjects in each group before and after treatment. Meanwhile, to avoid noise data outside the brain tissue in the results, BrainMask_61 × 73 × 61. img was selected as the whole - brain mask file. The statistical threshold was set at P < 0.005, and the minimum activation cluster was required to be larger than 20 voxels. The results of the regional homogeneity changes in the brain regions before and after treatment were obtained respectively.

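### The 21 per arm rest on a minimum for an fMRI network analysis that the article does not describe, and the claim of stable power is unsupported for the primary outcome IELT

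*Protocol article*

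**What the plan says.** All references are to the protocol article.

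- **Outcomes (Abstract).** "The primary outcomes are Intravaginal ejaculatory latency time (IELT) and Pre- and post-treatment brain fMRI scans". IELT is therefore a declared primary outcome alongside imaging.
- **Sample size (Study design).** "According to the minimum requirements for network analysis of functional neuroimaging studies, 15 subjects were needed in each group". Then "21 subjects were included in each group to ensure the credibility of the study results", with the reason "taking into account the unavailability of data due to patient dropout and head movement during scanning". No loss rate is given. A second basis for the total of 84 begins "Through previous studies and in combination with the actual situation of the project" and carries a citation but no numbers.
- **Power (Discussion, Sample Size Determination).** "To achieve stable statistical power, the sample size is carefully planned". The next sentence assigns 21 patients per group to clinical evaluation.
- **Imaging analysis (Regional homogeneity analysis).** "First, a paired t - test was used for the comparative analysis of the ReHo images", run within each APE group before and after treatment. The section before it defines ReHo as the concordance of each voxel with its 26 neighbours.
- **Aims (end of Introduction).** The first aim says, of the comparison with placebo and paroxetine, that "CHSGS will be as the same effective to the treatment for APE". The second expects CHSGS and the combination to do better than paroxetine alone. Both are between-arm efficacy statements.
- **Testing (Clinical variables analysis).** A list of methods, including an independent-samples t-test and analysis of covariance, two-sided testing, and P below 0.05 as the only criterion. No equivalence or non-inferiority margin is stated.

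**The concern.** Three statements do not fit together. The number comes from a minimum for network analysis, but the imaging analysis set out is a local, voxelwise measure tested within arms. The number is then presented as giving stable power and is tied to clinical evaluation, although no clinical quantity entered its stated derivation. And the aims that depend on between-arm IELT differences have no stated difference, SD or margin.

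What is at stake is how the IELT results will be read. The first aim is a claim of equal effect, and the plan offers only significance tests. The route this leaves to that claim is a non-significant CHSGS-paroxetine difference. A reader told that power is stable has reason to accept such a result as evidence of equal effectiveness, when the interval around it may be wide.

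**Working it through.** **Inputs from the article:** 21 per arm; 15 as the stated minimum; four arms, 1:1:1:1; two-sided 5%; independent-samples t-test among the listed methods.

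**Not in the article:** IELT effect, IELT SD, equivalence margin, target power. Differences are therefore expressed in SD units (d = difference / SD), and 80% power is assumed as the usual target.

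**1. The plan's own figures.** The 15 is a rule of thumb with no inputs, so it cannot be recomputed. The step from 15 to 21 implies a loss of 1 − 15/21 = 28.6%; a 20% loss would have given 15/0.8 = 18.75, so 19. The total 4 × 21 = 84 is correct.

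**2. Detectable IELT difference, one pairwise contrast.** Normal approximation: d = (1.960 + 0.842) × √(2/n).
- n = 21: 2.802 × 0.3086 = 0.865; with the noncentral t, 0.886, about **0.89 SD**.
- n = 15: 2.802 × 0.3651 = 1.023; with the noncentral t, **1.06 SD**.

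**3. Allowing for several contrasts.** The first two aims name three distinct contrasts: CHSGS vs placebo, CHSGS vs paroxetine, and combination vs paroxetine. If Bonferroni over three were used (an assumption; the article states no adjustment), alpha = 0.05/3 = 0.0167. The detectable difference is then 1.04 SD at n = 21.

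**4. Power across assumed true differences** (noncentral t, unadjusted 5%):

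| True difference (SD) | 21 per arm | 15 per arm |
|---|---|---|
| 0.3 | 16% | 12% |
| 0.5 | 35% | 26% |
| 0.8 | 72% | 56% |
| 1.0 | 89% | 75% |
| 1.2 | 97% | 89% |

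For 80% power at 0.5 SD, 64 evaluable per arm would be needed.

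**5. Precision.** The 95% CI half-width for one contrast at n = 21 is t(0.975; 40 df) × √(2/21) = 2.021 × 0.3086 = **0.62 SD**.

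**6. Equal effect (aim 1).** Two one-sided 5% tests, true difference 0, 80% power: margin ≈ [t(0.95; 40) + t(0.90; 40)] × √(2/21) = (1.684 + 1.303) × 0.3086 = **0.92 SD**. At n = 15 (28 df): (1.701 + 1.313) × 0.3651 = 1.10 SD.

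**7. Non-significance as a route to aim 1.** If CHSGS and paroxetine truly differed by 0.5 SD, the test at 21 per arm would miss it with probability 1 − 0.35 = 65%.

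**8. Effect of baseline adjustment.** Analysis of covariance is among the listed methods. With an assumed baseline correlation of 0.5, the detectable difference at n = 21 falls to 0.886 × √(1 − 0.25) = 0.77 SD.

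**The case against.** The strongest reply is that low power has not been demonstrated. With no IELT effect or SD in the article, actual power is unknown. At 21 per arm a true difference of 1.0 SD has 89% power, and an active-versus-placebo contrast might be that large. This stands. A reader might infer that the trial is underpowered for IELT; the article supports only that its power statement has no shown basis.

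Four further objections stand in part.

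- **Fifteen is an imaging floor.** The allowance from 15 to 21 covers head movement as well as dropout, and head movement does not spoil a stopwatch measurement. The number with usable IELT should exceed 15 if the allowance is right. The n = 15 figures are a worst case, not the expected IELT sample.
- **Multiplicity and adjustment are open.** Correcting for all six pairwise contrasts (1.12 SD at 21 per arm) would go beyond the aims, which name three. Covariate adjustment could improve matters, as step 8 shows, but the correlation is an assumption.
- **The second basis for 84.** It cites previous studies, and whether they concerned IELT cannot be seen. It supplies no numbers, so it neither supports nor refutes the power statement.
- **The article is condensed.** A reader might infer that no network analysis will be run. The imaging account is visibly incomplete: it announces a first step and gives no second, and it covers neither the between-intervention comparison nor the healthy controls. The supportable statement is that the article describes none.

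Condensation does not answer the point itself. The network-analysis basis and the power statement are the article's own sentences, and they do not fit the analyses it describes. It is also fair that no sentence says non-significance will be taken as equality, and that the first aim is awkwardly worded. The equivalence margin above rests on reading it as equal effect with paroxetine.

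**Conclusion.** The concern holds in a limited form. The stated basis for the sample size belongs to a type of imaging analysis that the article does not describe, and the statement of stable power is unsupported for IELT and for the between-arm aims. At 21 per arm, 80% power exists for a single contrast only from about 0.89 SD, about 1.04 SD if three contrasts share the 5%, or about 1.06 SD unadjusted if only 15 were evaluable. The contrasts most exposed are those with paroxetine, where both arms are active, and the claim of equal effect.

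These figures assume a t-test on approximately normal data with equal SDs, two-sided 5% and an 80% target. They cannot be turned into minutes without an SD. They do not show that an active-versus-placebo comparison is inadequately powered, and they give no reason to demote the declared primary fMRI outcome or to impose a single confirmatory contrast. Those would be separate design decisions.

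**What to change.** Keep 84 patients.

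1. In Study design and in the Discussion's sample-size paragraph, replace the network-analysis basis and the stable-power statement. Say that the size is feasibility-based, and that 21 per arm gives 80% power (two-sided 5%, unadjusted t-test) for an IELT difference of about 0.89 SD, or 1.06 SD in the worst case of 15 evaluable.
2. In Clinical variables analysis, state that between-arm IELT differences will be reported with 95% confidence intervals, with an expected half-width of about 0.62 SD at 21 per arm.
3. State there, and beside the first aim, that a non-significant CHSGS-paroxetine difference will not be taken as equal effectiveness.

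The cost is a less favourable stated justification and a weaker conclusion under the first aim. Recruitment, treatment and data collection do not change.
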